### Intervention

First stage: probiotic bacteria, *L. reuteri* (BioGaia), will be used in the study. It has been used in previous clinical trials, including those targeting pediatric populations [20–22]. Subjects will receive 10^10^ colony-forming units of *L. reuteri* daily or placebo for a duration of 3 months. *L. reuteri* has demonstrated consistently favorable safety profiles across multiple clinical trials [20–22].

Second stage: We chose to use syntocinon intranasal spray (Novartis pharmaceuticals) as it is currently the most commonly used standardized oxytocin nasal spray for clinical trials worldwide. Because patients with sensory difficulties need additional training, we will instruct the patient and family members to the use of spray, which begins with 1 puff of 4 IU daily, as well as provide training for MRI taking. After 1 week, the dose will increase to 1 puff per nostril for both nostrils daily (8 IU/day). After the second week, the dose will increase to 1 puff per nostril for both nostrils twice a day (16 IU/day). After the third week, the dose will titrate up to the maximum dose 24 IU daily, which is 2 puffs per nostril for both nostrils in the morning, and 1 puff per nostril for both nostrils in the afternoon. The dosage of 24 IU per day has been approved safe and adequate in even younger patients (ages 3–8 years old) by previous publications [23, 24].

### Outcomes

#### Primary outcomes

Social and behavioral scores assessed using behavioral assessment questionnaires validated in ASD, including the Aberrant Behavior Checklist (ABC) and Social Responsiveness Scale-2 (SRS-2). ABC is a 58-item behavior rating scale used to measure behavior problems across five subscales, which include irritability, lethargy/social withdrawal, stereotypic behavior, hyperactivity/noncompliance, and inappropriate speech. SRS-2 consists of 65 items used for quantitative assessment of the severity of ASD symptoms. The SRS-2 [25] is a caregiver completed rating scale assessing social interest and interaction. Scores from SRS-2 and ABC include composite summary scores and subscale scores (ABC: composite score scale = 0–174, social withdraw subscale = 0–48, stereotypical behavior subscale = 0–21, inappropriate speech subscale = 0–12; SRS-2: composite score scale = 0–195, social awareness subscale = 0–24, social cognition subscale = 0–36, social communication subscale = 0–66, social motivation subscale = 0–33, autistic mannerism subscale = 0–36).Objective ASD behavioral scores assessed by using eye-tracking test and emotional face matching tests. For eye-tracking test, fixation time for the eye and body area (continuous variable) will be calculated for data analysis (ASD reference range 0–2000 ms) [26]. For emotional face matching test, performance measures consist of reaction time (RT) (ASD reference range 8.18 ± 3.42 s) and accuracy (ASD reference range 62.5 ± 21.0%) [27].Baseline levels and increment of serum OXT levels by *L. reuteri* probiotics (ASD reference range 31.77-314.35 pg/ml) [8].

### Data collection

All data collection will be performed at 0 week (baseline), 12 weeks (end of *L. reuteri* probiotics-only stage), and 24 weeks (end of *L. reuteri* probiotics plus OXT dual therapy stage). Study data will be collected and managed using version v8.10.20 of REDCap (Research Electronic Data Capture) electronic data capture tools hosted at Massachusetts General Hospital. REDCap is a secure, web-based application designed to support data capture for research studies, providing (1) an intuitive interface for validated data entry, (2) audit trails for tracking data manipulation and export procedures, (3) automated export procedures for seamless data downloads to common statistical packages, and (4) procedures for importing data from external sources.

#### Baseline information

We will collect information regarding patients’ past medication history, immune functions, and lifestyle factors affecting the gut microbiome using questionnaires that have been published in a previous study that examined microbiome in ASD patients [28]. Immune questions include those pertaining to allergic symptoms and autoimmune disorders, and lifestyle questionnaire mainly includes factors affecting the microbiome (such as dietary habits).

#### ASD behavior assessment

ASD-related behavioral symptoms will be assessed by SRS-2 and ABC, which are two validated behavioral symptoms questionnaires widely used in ASD-related clinical trials. SRS-2 is a caregiver-completed rating scale assessing social interest and interaction. The scale provides a dimensional measure of social interaction allowing the rating of social skills in autism as well as non-autistic individuals. ABC is an informant rating instrument which resolves into five subscales, including irritability, lethargy/social withdrawal, stereotypic behavior, hyperactivity/noncompliance, and inappropriate speech.

#### Emotional facial matching test

We will use a previously validated emotional facial matching paradigm to objectively assess ASD patients’ ability to detect and characterize human emotions [27]. In this task, participants have to recognize a low-intensity and therefore ambiguous facial expression. Four expressions were used: happy, fearful, angry, and neutral. Dynamic morphs were created from the NimStim Emotional Face Stimuli database (http://www.macbrain.org/faces/index.htm#faces) between NEUTRAL and each EMOTIONAL expression using Morph Age Pro (http://www.creaceed.com/morphage/), and still images were created at 40% intensity level between neutral and the full emotional expressions. Participants will be then presented with one still image depicting happy, fearful, or angry at 40% intensity or NEUTRAL on the left side of the computer screen, while on the right still Ekman stimuli representing each of the four full emotional expressions were shown.

#### Eye-tracking test

We will use a new video-based eye-tracking device developed by Kong et al. [29] to objectively assess participants’ attention to human body parts. The paradigm consists of 10 video scenarios. Study subjects will be seated and allowed to watch a video containing moving geometric patterns on one side of an eye-tracking monitor and activities of human subjects on the other. The eye-tracking device records subjects’ eye gaze and characterizes the probability of the subject concentrating on geometric shapes or human subjects.

#### Assessments of GI health, GI microbiome, and short-chain fatty acid profiling

GI symptoms will be assessed by validated GI severity index (GSI) and Bristol Stool Chart; GI microbiome and metabolites and short-chain fatty acid profiling will be performed at the Microbiome core facility at Brigham and Women’s Hospital (Boston, MA). To quantify and analyze gut microbiome, 16S sequencing data will be processed and analyzed with the QIIME software package v. 2018.2.0. Alpha diversity will be calculated on the basis of the gene profile for each sample based on the Shannon index, Faith’s index, and Simpson’s evenness index. Beta diversity will be calculated on the unweighted and weighted UniFrac distances, Jaccard and the Bray-Curtis dissimilarity.

### Sample size and power calculation

This project is intended to evaluate the feasibility of implementing an oral supplementation of *L. reuteri* probiotics with and without an intranasal OXT spray therapy to inform an eventual larger-scale randomized trial that will allow for a more rigorous assessment of the efficacies of the proposed single or dual interventions. Hence, our sample size is calculated based solely on the primary outcomes: (1) scores of behavioral assessment questionnaires, including the ABC and SRS-2; (2) scores of objective ASD behavioral tests, including eye-tracking and emotional face matching tests; and (3) serum OXT changes. To achieve statistical power of 80% with an overall one-sided significance level of alpha = 0.10, if we assume a large effect size of 0.8 (Cohen’s *d*) in each of primary outcomes for the effect of *L. reuteri* probiotics alone vs *L. reuteri* probiotics plus OXT therapy, an estimated number of 26 ASD patients in each group would be needed based on independent two-sample *t* test. If a potential noncompliance or dropout rate of 10% is assumed, we plan to enroll 60 autistic subjects totally for this pilot study. Sample size calculation was carried out using the PASS 16 Power Analysis and Sample Size Software (NCSS, LLC. Kaysville, Utah).

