### Data management and statistical analysis plan

The principal investigator and co-investigators will monitor data as it is acquired to ensure the quality of the data. Data monitoring and auditing will be performed on a monthly basis on RedCap. All information regarding experimental patients will be kept in a file cabinet in the office of the principal investigator. All data for presentation will be identified by a code number only. All data spreadsheets will be housed on the password-protected server at the lab and de-identified as described above. All MGH collaborators will have access to the de-identified data as needed for analysis and manuscript preparation.

For statistical analysis, we will assess intervention credibility and acceptability and track the number of patients who meet the study criteria, the number approached for enrollment, the number enrolled, reasons why patients chose not to participate, dropout rate, and reasons for dropout. These data will be summarized by standard descriptive statistics. For all participants in the trial, descriptive statistics will be provided to characterize recruited patients at baseline for treatment and control groups and ensure that balance is achieved by randomization. The presentation of the data will follow the CONSORT recommendations for reporting results of RCTs. Statistical procedures carried out use *α* = 0.10 as the significance level. All analyses will be performed using SAS, version 9.4 (SAS Institute, Inc.).

Although this is a pilot study, we do want to explore whether or not there is a difference between groups. Analyses based on the intent-to-treat principle are designed to examine the treatment effect of *L. reuteri* probiotics vs placebo at the end of the first stage of trial on primary outcomes, which are behavioral scores (i.e., ABC and SRS-2), behavioral testing results (i.e., eye-tracking and emotional face matching tests), and serum OXT changes. Since there are multiple primary outcomes, false discovery rate due to multiple comparisons will be taken into account. Per-protocol analyses for secondary outcomes will be performed based on available data due to relatively small sample size. Methods for secondary analyses conducted will be similar to primary analyses. Two-sample *t* tests will be performed on secondary outcomes as appropriate.

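### The stated inputs do not lead to 26 per group: one test at one-sided 0.10 needs 15, and any split of the overall alpha is not printed

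*Protocol article*

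**What the plan says.** In the Protocol article, Sample size and power calculation, the target is set as "To achieve statistical power of 80% with an overall one-sided significance level of alpha = 0.10". The effect is given as "if we assume a large effect size of 0.8" (Cohen's d), applied to each primary outcome. The result is "an estimated number of 26 ASD patients in each group would be needed based on independent two-sample" t test. An allowance of 10% for noncompliance or dropout then leads to 60 patients in total.

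The same section numbers three groups of primary outcomes: questionnaire scores (ABC and SRS-2), objective tests (eye-tracking and emotional face matching) and serum OXT change. That makes five named measures. It prints no per-test alpha and no number of tests.

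Data management and statistical analysis plan says "Statistical procedures carried out use *α* = 0.10 as the significance level", without saying whether this is one- or two-sided. It adds that the false discovery rate will be considered because there are several primary outcomes.

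**The concern.** Power, alpha, sidedness, effect size and test are all printed, so a reader should be able to recover the 26. Taken at face value for one test, they give a much smaller number. The word "overall one-sided significance level" points to several tests sharing the 0.10, but the article does not say how many tests or how the level is shared.

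At stake is what the stated 80% refers to. If each outcome is tested at one-sided 0.10, the power at d = 0.8 is well above 80%. If 0.10 is shared over all five measures, it is slightly below 80%. A larger trial is to be designed from this pilot, and its planners need to know which error rate and which power the pilot was built on.

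**Working it through.** **Inputs, all from Sample size and power calculation:** power 80%, one-sided alpha 0.10 called overall, d = 0.8, independent two-sample t test, 26 per group, 10% dropout. Equal allocation (1:1) comes from Study design.

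**Formulas.** The normal approximation for n per group is n = 2(z₁₋α + z₀.₈₀)² / d². The exact figures below use the noncentral t distribution with 2n − 2 degrees of freedom and noncentrality d√(n/2). The n reported is the smallest that reaches 80% power.

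**Step 1: the printed inputs on one test.** n = 2(1.2816 + 0.8416)² / 0.64 = 2 × 4.508 / 0.64 = 14.1, so 15. The exact calculation also gives 15 (power 0.810). With 26 per group the power is 0.943, and 80% power is reached at d = 0.594.

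**Step 2: which level returns 26 at d = 0.8?** At one-sided 0.025, n = 2(1.9600 + 0.8416)² / 0.64 = 2 × 7.849 / 0.64 = 24.5, so 25. The exact t calculation gives 26, with power 0.8075. This is the same calculation as two-sided 0.05.

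**Step 3: sharing an overall one-sided 0.10 equally over k tests.**

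| k | per-test one-sided alpha | exact n per group | power at 26 per group |
|---|---|---|---|
| 1 | 0.10 | 15 | 94.3% |
| 2 | 0.05 | 21 | 88.5% |
| 3 (numbered domains) | 0.0333 | 24 | 84.2% |
| 4 | 0.025 | 26 | 80.7% |
| 5 (named measures) | 0.02 | 28 | 77.9% |

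A Šidák split, with per-test level 1 − 0.9^(1/k), gives 23, 26 and 27 for k = 3, 4 and 5. Reading 0.10 as two-sided on one test gives 21. So with d held at 0.8, equal sharing returns 26 only for k = 4.

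**Step 4: does a different input explain it?** Keeping one-sided 0.10 on one test and 80% power, d = 0.6 also gives 26, but the text says 0.8. Several changes of input can therefore produce 26, and the article does not show which calculation was run.

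**Step 5: from 26 to 60.** 26 / 0.90 = 28.9, so 29 per group and 58 in total. The planned 60 covers this, so the dropout step is sound.

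**Step 6: compare with the analysis section.** It tests at 0.10 and handles multiplicity through the false discovery rate. A fixed division of 0.10 by four is a different rule, so even the split that returns 26 is not the rule announced for the analysis.

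**The case against.** The strongest defence is that the alpha is called overall and that d = 0.8 is assumed for each of several primary outcomes. A familywise 0.10 divided by four is 0.025, which returns exactly 26. A count of four can be found: the Methods paragraph of the Abstract names serum OXT, the two questionnaires joined together, the face matching test and the eye-tracking test. Counts of three and five also land within two patients of 26. Study design gives a separate reason for 30 per arm (acceptability and tolerability), and between-group testing is described as exploratory.

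Much of this stands. The four-way split cannot be excluded, so a reader who infers that 26 is simply an error, or that two-sided 0.05 must have been used, goes further than the document allows. It does not follow either that results might be judged at 0.025, with a four-fold uncertainty in the false-positive rate. The analysis section fixes 0.10, and only its sidedness is open.

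What does not stand is that the defence makes the statement verifiable. The divisor is not printed. Four is reached only by merging the two questionnaires while keeping the two objective tests apart, whereas the sample-size section groups both pairs. Being close to 26 is also not the same as yielding it: 24 would suffice for three tests, and 26 falls short of 80% for five.

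**Conclusion.** The concern holds in this form: 26 per group does not follow from the inputs as printed. One test at one-sided 0.10 needs 15, and 26 then gives 94% power at d = 0.8, or 80% at d = 0.59. The printed 80% matches 26 at one-sided 0.025, a level the article never states. On its own outcome counts the required n is 24 or 28, and for five measures 26 gives 77.9%.

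These figures rest on equal groups, a t test with common variance, d = 0.8 and, for the split, equal sharing of 0.10. They show that the statement is incomplete or inconsistent, not which calculation produced it.

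The trial is not undersized on the single-test inputs, since 26 exceeds 15. This is a correction to a stated figure and does not call for a change in enrolment.

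**What to change.** Keep N = 60. Check the inputs of the original software run, then restate Sample size and power calculation so that alpha, sidedness, number of tests, power and n agree. There are two ways to do so:

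- Keep one-sided 0.10 per test, and state that 26 per group gives 94% power at d = 0.8, or 80% power at d = 0.59.
- Print the per-test alpha and the number of primary tests actually used, with the power that 26 per group gives: 80.7% at one-sided 0.025, or 77.9% at 0.02 for five measures.

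In Data management and statistical analysis plan, state whether the 0.10 is one- or two-sided, and keep it consistent with the sample-size text. If a split was used for sizing, say how it relates to the false discovery rate control planned for the analysis. The analysis level should not be moved to two-sided 0.05 merely because that happens to reproduce 26. That would change the declared decision rule on a guess.

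The cost is a wording change in two paragraphs, best made before any outcome data are analysed.

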### Study procedure

The treatment will proceed for a total of 24 weeks (Fig. 1 and Table 1). In the first stage (12 weeks), all the patients will be randomly assigned to two groups: group A (30 subjects) receives oral *L. reuteri* probiotics while group B (30 subjects) receives oral as a placebo. We decided on a 12-week timeline because according to the most recent systematic review of probiotics therapy in ASD, the average duration of clinical trials is 3 months [19]. In the second stage, subjects in group A and group B will continue their respective oral *L. reuteri* probiotics or placebo administration as in stage 1. In addition, both groups will be simultaneously administered with intranasal OXT spray for an additional 12 weeks. We will stratify patients according to their ASD severity based on screening questionnaires and diagnostic evaluations.

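### The 80% power claim is attached to L. reuteri alone versus L. reuteri plus OXT, a contrast the design does not provide; the analysed contrast, L. reuteri versus placebo at week 12, has no stated effect size or power

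*Protocol article*

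**What the plan says.** **Sample size and power calculation.** The error rates come first: "To achieve statistical power of 80% with an overall one-sided significance level of alpha = 0.10". The effect follows: "if we assume a large effect size of 0.8" (Cohen's d) in each primary outcome. It is assigned to L. reuteri "probiotics alone vs *L. reuteri* probiotics plus OXT therapy". The same sentence then gives the result: "probiotics plus OXT therapy, an estimated number of 26 ASD patients in each group would be needed based on independent two-sample" t test. The total comes from an allowance for loss: "If a potential noncompliance or dropout rate of 10% is assumed, we plan to enroll 60 autistic subjects totally for this pilot study".

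**Study design, Study procedure and Table 1.** Sixty patients are allocated 1:1 to L. reuteri (group A) or placebo (group B). In the second stage each group keeps its capsules, and "both groups will be simultaneously administered with intranasal OXT spray for an additional 12 weeks". Table 1 gives the second-stage comparison as L. reuteri plus OXT spray against placebo plus OXT spray.

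**Data management and statistical analysis plan.** The intent-to-treat analysis of the primary outcomes examines L. reuteri "vs placebo at the end of the first stage of trial on primary outcomes". The significance level is 0.10, with no side stated. The false discovery rate is to be considered across the several primary outcomes.

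**The concern.** A sample-size statement should be about the comparison that the trial randomises and analyses. Here it is about another one. No group is randomised to L. reuteri alone alongside a group on L. reuteri plus OXT. Group A has the first condition in weeks 0–12 and the second in weeks 13–24; group B has neither. An independent two-sample t test does not fit two periods in the same people, and any difference between the periods would be mixed with the passage of time and with longer exposure to L. reuteri.

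The effect-size assumption is also at stake. A d of 0.8 for adding OXT to L. reuteri says nothing about L. reuteri against placebo. A reader who takes 80% as the power of the week-12 test has no stated basis for doing so. This matters because the paragraph says that the sample size rests solely on the primary outcomes.

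**Working it through.** **1. Which contrasts exist**

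| Contrast | Who is compared | Randomised? | Where it appears |
|---|---|---|---|
| L. reuteri vs placebo, week 12 | group A vs group B | yes | Table 1; analysis section |
| L. reuteri + OXT vs placebo + OXT, week 24 | group A vs group B | yes | Table 1 |
| L. reuteri alone vs L. reuteri + OXT | group A at week 12 vs group A at week 24 | no; same patients | sample-size paragraph only |

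The article describes no test for the third row, yet that row carries the power statement.

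**2. The plan's own figure**

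Inputs from the sample-size paragraph: d = 0.8, power 80%, independent two-sample t test, overall one-sided alpha 0.10, 10% loss. With n per group, power is the probability that a noncentral t variable with 2n − 2 degrees of freedom and noncentrality d·√(n/2) exceeds the critical value t(1 − α, 2n − 2).

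- One-sided 0.10 as written: n = 14 gives 78.9% and n = 15 gives 81.0%, so 15 per group are enough. At n = 26 the power would be 94.3%.
- One-sided 0.025 (assumption): n = 25 gives 79.2% and n = 26 gives 80.8%, so 26 per group.
- One-sided 0.025 is what results from splitting 0.10 over four outcomes (0.10/4), and it also equals two-sided 0.05. The article states neither. Splits over three or five outcomes give 24 and 28.

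So 26 is reproduced only with a per-outcome alpha that the article does not state. That makes 26 unexplained, not proven wrong.

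Loss: 26/0.9 = 28.9, rounded up to 29 per group, or 58 in total. The planned 60 covers this. In the other direction, 30 × 0.9 = 27 evaluable per arm.

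**3. The contrast that will be analysed: L. reuteri vs placebo, 27 per arm**

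Same formula, 52 degrees of freedom. Critical values are 1.298 (one-sided 0.10) and 2.007 (one-sided 0.025). The article gives no d for this contrast, so both values below are assumptions.

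| d (assumed) | Noncentrality d·√(27/2) | Power, one-sided 0.10 (stated, overall) | Power, one-sided 0.025 (assumed) |
|---|---|---|---|
| 0.8 | 2.939 | 94.9% | 82.2% |
| 0.5 | 1.837 | 70.6% | 43.8% |

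The d detectable with 80% power is 0.58 at one-sided 0.10 and 0.78 at one-sided 0.025.

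**4. The contrast as literally named**

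Within group A the comparison is paired: dz = 0.8/√(2(1 − ρ)), where ρ is the within-person correlation, which the article does not give. With 27 patients and ρ = 0 (assumption), dz = 0.566, and power is 94.6% at one-sided 0.10 or 80.8% at an assumed one-sided 0.025. A positive correlation raises both. Shortage of power is therefore not the problem with this contrast. The problem is that it has no concurrent control and is not what the t test in the paragraph describes.

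**The case against.** The strongest reply is that this is a drafting slip. The Secondary outcomes section uses nearly the same labels for the two stages of the trial, and the reference to each group, the two-sample t test and a total of 60 (2 × 30) all fit the two randomised arms. The authors may have meant the effect of either regimen against its control. That is plausible, and it limits the consequence: relabelling the contrast leaves the t-test arithmetic unchanged if d = 0.8 is kept, the analysis section already names the valid randomised comparison by intent to treat, and the trial is a feasibility pilot whose efficacy comparison is exploratory. The second-stage comparison between arms is also already in Table 1, and further week-24 analysis detail may stand in a fuller document.

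All of that stands. It does not rescue the sentence, which assigns the effect size to a specific contrast that contradicts the design in the same article. A fuller document could add detail but would not make the printed statement correct.

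A reader might infer more: that the trial will compare group A's week-12 and week-24 values as if they came from different people, or that it is underpowered because of the mismatch. The article supports neither. It plans no test of week 12 against week 24 within group A, and power at d = 0.8 with 27 evaluable patients is above 80% under each alpha and correlation considered here.

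**Conclusion.** The sample-size paragraph is wrong as written: it attaches d = 0.8, 80% power and 26 per group to two successive periods in the same patients, while the contrast to be analysed has neither an effect size nor a power. It is an error in the justification of the sample size. It corrupts no planned analysis and does not by itself alter the 60 patients.

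The power of the week-12 test cannot be read from the article. With 27 evaluable per arm it runs from about 95% (d = 0.8, one-sided 0.10) to about 44% (d = 0.5, one-sided 0.025). Both values of d are assumptions for this contrast. The 0.025 level is also an assumption, chosen because it reproduces 26; only the overall one-sided 0.10 is stated.

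**What to change.** Rewrite the sample-size paragraph for L. reuteri versus placebo at week 12. It should give:

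- the alpha applied to each primary outcome and whether it is one- or two-sided, in agreement with the analysis section;
- the d assumed for this contrast and the reason for it;
- the resulting power with 27 evaluable patients per arm.

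The power cannot be stated until the first two items are settled, so changing only the names of the treatments would not be enough.

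Keep L. reuteri plus OXT versus placebo plus OXT at week 24 as the second between-arm comparison, as Table 1 has it. If a week 12 to week 24 change within group A is reported at all, describe it as paired, uncontrolled and descriptive, and make no power claim for it.

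The cost is a revised paragraph. If d = 0.8 and the alpha behind 26 are confirmed for this contrast, enrolment stays at 60; data collection and the planned week-12 analysis are unaffected.
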